## Abstract

Faecal microbiota transplantation (FMT) is an emerging therapy for gastrointestinal and neurological disorders, acting via the microbiota–gut–brain axis. Altering gut microbial composition may influence cognitive function, but this has not been tested in cognitively healthy adults. This randomised, double-blinded, placebo-controlled pilot trial investigates whether FMT is feasible and improves cognition in adults with irritable bowel syndrome (IBS). Participants receive a single dose of FMT or placebo via rectal retention enema. Cognitive performance is the primary outcome, assessed using the Cambridge Neuropsychological Test Automated Battery (CANTAB). Secondary outcomes include IBS symptom severity and mood. Tertiary outcomes include microbiome composition and plasma biomarkers related to inflammation, short-chain fatty acids, and tryptophan metabolism. Outcomes are assessed at baseline and at one, three, six, and twelve months following treatment. We hypothesise that FMT will lead to greater improvements in cognitive performance than placebo, with benefits extending beyond practice effects, emerging at one month and persisting in the long term. The findings will contribute to evaluating the safety and efficacy of FMT and enhance our understanding of gut–brain interactions.

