Stool donors will be screened in accordance with TGA guidelines (Therapeutic Goods Order 105) for human intestinal microbiota transplants. Eligible donors are healthy adults with no history of chronic gastrointestinal disorders, infectious diseases, recent antibiotic use, or high-risk behaviours. Screening includes a detailed social and medical history, physical examination, and laboratory testing of both blood and stool samples. Blood tests include screening for HIV-1 and HIV-2, hepatitis A, B, and C, syphilis, HTLV-I/II, and other transfusion-transmissible infections. Stool samples are tested for common enteric pathogens, including *Clostridioides difficile*, *Salmonella*, *Shigella*, *Campylobacter*, *Giardia*, *Cryptosporidium*, and norovirus, as well as for antimicrobial-resistant organisms, such as extended-spectrum beta-lactamase-producing bacteria. Donors are also screened for COVID-19. All screening procedures are repeated every 90 days during the donation period.

Participants will return for follow-up assessments at one, three, six, and twelve months following treatment (see Figure 2). At each time point, they will complete all questionnaires and cognitive tests and provide stool and blood samples.

This pilot trial will assess the feasibility of the protocol and provide preliminary estimates of the effect size. Cognitive performance, inflammatory markers, and microbial metabolites will be analysed using mixed-design ANOVA, with group (FMT vs. placebo) as the between-subjects factor and time (baseline, one, three, six, and twelve months) as the within-subjects factor. Planned contrasts will examine within-group changes over time. Microbiome composition will be compared using PERMANOVA with Bray–Curtis dissimilarity, and missing data will be addressed using multiple imputation.

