### 2.1. Outcome Measures

This protocol includes outcome measures across three domains. These outcomes will be analysed to assess feasibility, identify sensitive indicators of cognitive change, and guide the design of future trials.

Primary outcome: Cognitive performance, assessed using the Cambridge Neuropsychological Test Automated Battery (CANTAB), which includes subtests for memory, attention, processing speed, and executive function.Secondary outcomes: Mood, measured using the Depression Anxiety Stress Scale (DASS-42), and IBS symptom severity, measured using the IBS Symptom Severity Score (IBS-SSS). The IBS Quality of Life (IBS-QoL) questionnaire is administered but will not be analysed in this sub-study.Tertiary outcomes: Stool-based gut microbiome composition and function (via shotgun metagenomic sequencing and SCFA quantification) and plasma-based biomarkers, including pro-inflammatory cytokines, short-chain fatty acids, and tryptophan metabolites.

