## 4. Expected Results

We expect cognitive performance in the placebo group to remain stable or show minor improvements over time due to practice effects. In contrast, participants receiving FMT may exhibit changes in cognitive function, including improvement or variability, reflecting the exploratory nature of this intervention in a cognitively healthy population. The expected cognitive changes may include faster reaction times, improved memory accuracy, or enhanced executive functioning.

Biological markers are anticipated to remain unchanged in the placebo group but may shift in the FMT group, consistent with microbiome modulation. These may include increased gut microbial diversity, reduced circulating pro-inflammatory cytokines, such as IL-6 and TNF-α, and shifts in short-chain fatty acid and tryptophan metabolite concentrations.

If the protocol is unsuccessful, the cognitive scores are expected to remain unchanged or decline slightly, and biological markers would show no consistent or directional changes over time. A full description of the outcomes assessed (including cognitive, psychological, microbial, and biochemical variables) is provided in Section 2 (Experimental Design).

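### The only contrasts the plan names are within-group changes, which mix practice gains with any FMT effect; the between-arm hypothesis needs FMT-minus-placebo contrasts

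*Protocol article*

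**What the plan says.** The hypothesis in the Abstract compares the arms and is specific about timing: "We hypothesise that FMT will lead to greater improvements in cognitive performance than placebo, with benefits extending beyond practice effects, emerging at one month". The same sentence goes on to claim long-term persistence.

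Section 2 (Experimental Design) assigns the cognitive scores, the inflammatory markers and the metabolites to one model: "analysed using mixed-design ANOVA, with group (FMT vs. placebo) as the between-subjects factor". The other factor is visit, with five levels: baseline and the four follow-ups. The next sentence is the only one on contrasts: "Planned contrasts will examine within-group changes over time". The section does not name the group-by-time interaction as the test of the hypothesis, and it names no between-arm contrast at any visit. It also says that the pilot is to give preliminary estimates of effect size.

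Section 4 (Expected Results) allows for stable scores or small practice-related gains in the placebo arm. It then describes an unsuccessful outcome: "If the protocol is unsuccessful, the cognitive scores are expected to remain unchanged or decline slightly".

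**The concern.** The hypothesis makes three claims: FMT does better than placebo, the advantage appears at one month, and it lasts. Contrasts are the usual tool for claims of that kind, because an overall F test does not address them one by one. The contrasts chosen here do not use the placebo arm. In a trial with five CANTAB sittings, the placebo arm is what separates practice from treatment.

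Two things are at stake. First, a significant change in the FMT arm, or a significant change there alongside a non-significant one in the placebo arm, could be read as benefit although that contrast makes no comparison between arms. Second, the pilot is meant to supply an effect size for a larger trial. A within-arm change used for that purpose would be too large by the amount of the practice gain.

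The wording of failure in section 4 adds to the risk. An inert treatment with ordinary practice gains need not look unchanged or slightly worse, so practice alone could be taken as a sign of success.

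**Working it through.** The documents give no alpha, SD, correlation or practice size, so there is no stated figure to reproduce. What follows is an illustration.

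**Inputs from the protocol article**
- 10 participants per arm (section 2).
- Five time points: baseline and four follow-ups (section 2).
- Practice gains possible in the placebo arm, size not given (section 4).

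**Assumptions**
- Two-sided alpha 0.05 and complete data.
- Equal correlation r between visits, from 0.6 to 0.8.
- A practice gain g of 0.2 to 0.3 SD, the same in both arms and at every follow-up.
- An FMT effect of exactly zero.

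**What each contrast estimates**
- Within FMT: practice + FMT effect = g + 0 = 0.2 to 0.3 SD.
- FMT minus placebo in change: (g + 0) − g = 0.

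Used as an effect size, the within-arm change is therefore too large by g.

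**One month, exact calculation**

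The SD of change is √(2(1 − r)), so the standardised change is dz = g/√(2(1 − r)). The paired t test has 9 df and noncentrality dz·√10.
- r = 0.6, g = 0.2: dz = 0.2/√0.8 = 0.224, noncentrality 0.71, chance of significant improvement 9%.
- r = 0.8, g = 0.3: dz = 0.3/√0.4 = 0.474, noncentrality 1.50, chance 27%.

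The arms are independent. If p is the chance of significant improvement in one arm, the chance that FMT is significant and placebo is not is about p(1 − p):
- 0.093 × 0.907 = 0.084, or 8%.
- 0.269 × 0.731 = 0.197, or 20%.

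With no practice gain, the within-arm chance of significant improvement is 2.5%.

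**Simulation, 20,000 trials per setting, same assumptions**

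| Quantity | r = 0.6, g = 0.2 | r = 0.8, g = 0.3 |
|---|---|---|
| Within-FMT improvement significant, one month | 9% | 27% |
| FMT significant, placebo not, one month | 8% | 20% |
| FMT significant at some visit, placebo at none | 19% | 25% |
| Between-arm contrast of change, one month (two-sided) | 5% | 5% |
| Group-by-time F test | 5% | 5% |

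Of the two-sided 5% for the between-arm contrast, half would favour FMT.

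**The omnibus test**

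Its degrees of freedom are (2 − 1) × (5 − 1) = 4. It holds its error rate whatever the practice gain. A significant result says only that the two profiles over time differ somewhere. It does not say in which direction, whether at one month, or for how long.

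**The case against.** The strongest reply is that the plan does compare the arms. A two-factor mixed ANOVA with group and time ordinarily contains the interaction, and that test holds 5%. Contrasts run after it may merely describe the pattern, and the article sets no rule that they decide anything. If contrasts were read only after a significant interaction, FMT significant and placebo not at some visit would occur in only 2 to 3% of trials under the same assumptions. This stands. A reader might infer that the trial never compares FMT with placebo, and the documents do not support that. What remains is that the interaction is not named as the test, no reading order is given, and the contrasts that are named do not address the hypothesis.

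A second reply is that this is a pilot aimed mainly at feasibility, stated to be unpowered for small or moderate effects, and that an analysis plan not shown may say more. That lowers the stakes but does not remove the point. The article states which contrasts are planned, so this is not a matter of missing detail, and estimating an effect size is one of the pilot's stated purposes.

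Three stronger readings are tempting and should not be made:
- **A larger error rate.** Counting any visit at which FMT is significant and placebo is not gives 24 to 47%. That is four looks set against a single-visit 5%, and it includes trials in which placebo improved significantly at a different visit. The like-for-like figures are those in the table for one month.
- **Diet and regression to the mean.** Baseline follows a 21-day diet and later diet is uncontrolled, but nothing says that the diet stops at baseline or that it affects cognition. IBS-SSS is not among the outcomes that section 2 assigns to this ANOVA, so an argument about regression to the mean in that score does not attach here.
- **Section 4 as a decision rule.** It is a loosely worded narrative of expectations. Since it allows stable placebo scores, an inert treatment could fit its description of failure; it just need not.

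**Conclusion.** The point holds as a mismatch between hypothesis and contrasts. The within-group contrasts cannot test greater improvement than placebo, because any gain shared by both arms enters them in full. The available interaction test is valid but unnamed, and it cannot by itself establish direction, onset at one month or persistence.

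Under the stated assumptions, a treatment with no effect gives a significant within-FMT improvement at one month in 9 to 27% of trials and the pattern of FMT significant, placebo not in 8 to 20%, against about 5% two-sided for the between-arm contrast. FMT significant at some visit with placebo at none occurs in 19 to 25%.

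These sizes rest on the assumed correlation and practice gain. The direction does not: a shared gain raises the chance of significant improvement within an arm and leaves the between-arm contrast untouched. The figures concern cognition, where the protocol itself raises practice. For biomarkers it expects no shared shift ("Biological markers are anticipated to remain unchanged in the placebo group"), so there the case rests only on the contrast having to match the comparison of interest.

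This should be corrected before unblinding. It does not invalidate the design.

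**What to change.** In section 2, name the group-by-time interaction as the test of the hypothesis and replace the contrast sentence with wording such as:

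> Planned contrasts will estimate the FMT minus placebo difference in change from baseline, with 95% CI, at one month (key contrast) and at three, six and twelve months; within-group changes are descriptive only.

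Apply this to the cognitive, inflammatory and metabolite outcomes that the ANOVA covers. In section 4, describe an unsuccessful result as no difference between arms beyond shared practice effects.

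The cost is two or three sentences, with no new data or participants. The between-arm estimates will be less precise: with equal SDs and 10 per arm, the standard error of a difference in change is √2, about 1.41, times that of a within-arm change. A between-arm contrast reaches 80% power only for a standardised difference of about 1.32, which agrees with the article's own statement on power. The intervals should therefore be read as estimates for planning the larger trial.

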### 2.1. Outcome Measures

This protocol includes outcome measures across three domains. These outcomes will be analysed to assess feasibility, identify sensitive indicators of cognitive change, and guide the design of future trials.

Primary outcome: Cognitive performance, assessed using the Cambridge Neuropsychological Test Automated Battery (CANTAB), which includes subtests for memory, attention, processing speed, and executive function.Secondary outcomes: Mood, measured using the Depression Anxiety Stress Scale (DASS-42), and IBS symptom severity, measured using the IBS Symptom Severity Score (IBS-SSS). The IBS Quality of Life (IBS-QoL) questionnaire is administered but will not be analysed in this sub-study.Tertiary outcomes: Stool-based gut microbiome composition and function (via shotgun metagenomic sequencing and SCFA quantification) and plasma-based biomarkers, including pro-inflammatory cytokines, short-chain fatty acids, and tryptophan metabolites.

### 2.3. Equipment

iPad (7th generation, Apple Inc., Cupertino, CA, USA);−80 °C freezer (ThermoFisher Scientific, Waltham, MA, USA, TSX60086FA);LC-MS system (SCIEX QTRAP 7500);Proteomics for cytokines (Olink Target 48 cytokines).

## 3. Procedure

### 3.1. Intervention Preparation

Screen potential stool donors according to TGA Therapeutic Goods Order 105 for eligibility.Collect stool in a sterile bucket within 6 h after defaecation.Weigh stool.Mix stool with phosphate-buffered saline and ten per cent pharmaceutical-grade glycerol to reach a ten percent concentration of stool.Draw the resulting faecal suspension into 60 mL syringes labelled according to TGA Therapeutic Goods Order 107.Produce placebo by mixing glycerol and saline solution (ratio 5:1), 5 g fibre, and 2 mL food colouring per litre.Draw the resulting suspension into 60 mL syringes.Cover all syringes in aluminium foil to ensure blinding.Store at −80 °C.

### 3.2. Pre-Treatment Phase (~3 Weeks)

Recruit participants, provide study information, and obtain written informed consent (for the consent form, see Supplementary Materials).Conduct MoCA and confirm a score of ≥26.Refer potential participants to study dietician for introduction to low FODMAP diet.Study dietician supervises the diet for three weeks. Adherence is monitored through food diaries and weekly phone calls.Participants complete the IBS-SSS during their first appointment with the dietician and again after 21 days on the diet.Score IBS-SSS.

 **CRITICAL STEP** Only invite participants with a <50-point IBS-SSS reduction and a MocA score of >25 to the baseline visit.

### 3.3. Baseline Assessment (~2 h)

Administer CANTAB, DASS-42, and IBS-SSS.Draw blood (2 × 9 mL EDTA tubes).Provide participant with a stool sampling kit (see Supplementary File S2).Centrifuge whole blood samples at 4 °C for 10 min to obtain plasma. Aliquot plasma into 1.5 mL Eppendorf tubes and store at −80 °C.

 **CRITICAL STEP** Process whole blood samples within 60 min of collection.

### 3.4. Intervention Visit (~1 h)

Thaw FMT or placebo syringes in an ice bath for two hours.Collect stool sample from participant and store at −80 °C.Provide participant with a fresh stool sampling kit for use before the follow-up visit.Administer 60 mL of the assigned treatment via rectal retention enema while the participant lies in a left lateral position.

 **PAUSE STEP** Ask participants to remain in the lateral position for 20 min under medical supervision to ensure adherence.

### 3.5. Follow-Up Visits (1, 3, 6, 12 Months After Intervention)

Repeat questionnaires and cognitive tests (CANTAB, DASS-42, IBS-SSS).

Collect stool samples (self-collected at home within 24 h prior to visit) and draw blood samples on-site (2 * 9 mL EDTA tubes).

Centrifuge blood at 4 °C for 10 min to obtain plasma. Aliquot into 1.5 mL Eppendorf tubes and store at –80 °C.

Store all stool and plasma samples at –80 °C until analysis. Plasma will be analysed for pro-inflammatory cytokines via ELISA and for tryptophan metabolites and short-chain fatty acids via liquid chromatography–mass spectrometry (LC-MS).

## 4. Expected Results

We expect cognitive performance in the placebo group to remain stable or show minor improvements over time due to practice effects. In contrast, participants receiving FMT may exhibit changes in cognitive function, including improvement or variability, reflecting the exploratory nature of this intervention in a cognitively healthy population. The expected cognitive changes may include faster reaction times, improved memory accuracy, or enhanced executive functioning.

Biological markers are anticipated to remain unchanged in the placebo group but may shift in the FMT group, consistent with microbiome modulation. These may include increased gut microbial diversity, reduced circulating pro-inflammatory cytokines, such as IL-6 and TNF-α, and shifts in short-chain fatty acid and tryptophan metabolite concentrations.

If the protocol is unsuccessful, the cognitive scores are expected to remain unchanged or decline slightly, and biological markers would show no consistent or directional changes over time. A full description of the outcomes assessed (including cognitive, psychological, microbial, and biochemical variables) is provided in Section 2 (Experimental Design).

## Figures and Tables

**Figure 2 mps-08-00083-f002:**
[figure not shown]
Participant timeline. Screening procedure, diet phase, and cognitive and biomarker assessment at baseline and follow-ups in FMT and placebo groups. Participants are randomised to FMT or placebo, and all involved in data collection and treatment administration are blinded to the group allocation. Blue = recruitment/screening for eligibility; yellow = diet phase; pink = FMT group; green = placebo group.

## Data Availability

De-identified data supporting the findings of this study will be made available upon reasonable request from the corresponding author. Microbiome data will be deposited in a public repository following study completion. Access to participant-level data is restricted due to ethical and privacy considerations.

## Abbreviations

The following abbreviations are used in this manuscript:

ACTRN	Australian New Zealand Clinical Trials Registry Number
AD	Alzheimer’s Disease
CANTAB	Cambridge Neuropsychological Test Automated Battery
DASS-42	Depression Anxiety Stress Scale (42-item version)
ELISA	Enzyme-Linked Immunosorbent Assay
FMT	Faecal Microbiota Transplantation
IBS	Irritable Bowel Syndrome
IBS-QoL	IBS Quality of Life Instrument
IBS-SSS	IBS Symptom Severity Score
IL-6	Interleukin-6
LBP	Lipopolysaccharide-Binding Protein
LC-MS	Liquid Chromatography–Mass Spectrometry
MoCA	Montreal Cognitive Assessment
OTS	One-Touch Stockings of Cambridge
PAL	Paired Associates Learning
PRM	Pattern Recognition Memory
rCDI	Recurrent Clostridioides difficile Infection
RTI	Reaction Time
SCFA	Short-Chain Fatty Acid
SPIRIT	Standard Protocol Items: Recommendations for Interventional Trials
SWM	Spatial Working Memory
TGA	Therapeutic Goods Administration
TGO	Therapeutic Goods Order
VRM	Verbal Recognition Memory
